### Statistical power

The required sample size for the primary outcome (automaticity over time) was estimated based on recently published recommendations [78]. The power estimation revealed that a level-2-sample size with at least *N* = 228 participants (i.e., number of required individuals, accounting for 30% sample attrition) and a level-1-sample size of at least *n* = 13 measurement points (i.e., number of repeated measurements) is required to detect medium-sized population effects of *f* = 0.40 [21, 79] with sufficient power (≥ 0.80).

### Statistical analysis

Statistical analysis will be performed using SPSS Version 27 and conducted after completion of the data collection process. Interim analyses will not be performed. All primary outcome data will be screened for normal distribution by using the Shapiro–Wilk test. Data will be checked for outliers and missing data. Descriptive statistics will be run to explore the sample characteristics. Continuous variables will be presented as means and standard deviations, while categorical variables will be displayed by percentages of participants in each possible category. Intention-to-treat analyses will be conducted, given that drop-out rates are usually high in eHealth research [80], per protocol analysis are not feasible. Only data sets from participants who completed the baseline, post and 50% of the weekly assessments will be included in the analysis. To investigate difference between the sample of analysis and those who provided baseline data only, differences between baseline scores and a dichotomous attrition variable (i.e., 0 = not retained for analysis, 1 = retained) will be analyzed using χ^*2*^ and *t*-tests, followed by logistic regressions. To test for changes in habit strength, motivational (intention, self-efficacy, and outcome expectations), volitional constructs (action planning), health behaviors and health status from baseline to post assessments, analysis of variance with repeated measures and *t*-tests between subsequent measures will be run (hypothesis 1 a-e). To examine hypotheses 2–4, hierarchical multiple linear regression analyses will be conducted, with motivational, volitional and habit-related predictors at baseline to predict habit strength, health status and health behavior at post-assessment. To account for the hierarchically structure of data (i.e., repeated measurements nested within individuals) we plan to run two-level models with 13 assessment periods nested in participants (hypotheses 5 a-b, linear mixed models, LMM, [81]). LMM allows to test for simultaneous assessment of the effects of within-person variation in weekly assessments of behavior,habit strength and predictor variables (level 1) and between-person variables such as age, health status and other covaraites measured only once (level 2). Prior to running analyzes, the time parameters will be grand mean centered to minimize multicollinearity. Subsequently, various steps will be undertaken to determine appropriate model fit, as suggested by Field [81]. Once the model shows appropriate fit parameters, LMM can be conducted by selecting the Restricted Maximum Likelihood for estimation method [81]. In a model including all behavior-related cognitions and covariates simultaneously, motivational and volitional variables will be modeled at the between-person level (e.g., comparing persons with higher average versus lower average intentions) and the within-person level (e.g., assessments when intentions to engage in health behavior were higher-than-usual vs. lower-than-usual). Models will be run separately for each behavioral domain.

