### Evaluation design

A one-arm, multicenter mHealth interventional study will be performed. Participants complete all assessments in the app with the same assessment rhythm irrespective of when participants enroll in the study. Upon registration, participants can complete questions on socio-demographic variables, psycho-social determinants (e.g., intention, self-efficacy), physical activity, nutrition and mindfulness as well as health-related outcomes (e.g., back pain). Data will be collected across a 100-day period at four assessment points: baseline (booking date + 0), interim after 4 weeks (booking date + 28) and 8 weeks (booking date + 56) and post-intervention (booking date + 99). Additionally, 11 weekly assessments will be scheduled (booking date + 7, + 14, + 21, + 35, + 42, + 49, + 63, + 70, + 77, + 84, + 91). Participants will receive reminder emails for the baseline and post assessment four days after the respective assessment date (i.e., baseline reminder booking date + 4 days, post assessment booking date + 104 days). Reminders for the remaining assessments are incorporated into the app (via “open tasks”, see Description of the intervention for further information). Outcome data will be the same for all participants, whether they continue or discontinue/deviate from the intervention protocol. One week after the completion of the intervention, a structured interview is scheduled with volunteers to gain insights in participants’ experiences with the app (e.g., practicability, operability, acceptability). Due to economic reasons, the total set of items varies per assessment point. The Fig. 3 presents an overview of the enrolment schedule, the intervention, worksheets and assessments.

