Limitations. The study design is not without limitations. First, we are not able to collect participants for a control group, as the resources for this study are limited. Consequently, it is not possible to evaluate the effectiveness of the mHealth app. Furthermore, due to the uncontrolled design it is not possible to help close the knowledge gap pertaining to the question, as to whether traditional context-dependent repetition is necessary for habit formation or if it represents the most promising or reliable ingredient of habit formation interventions. Future studies are warranted to compare and evaluate habit formation interventions against non-habit based programs. Second, the mHealth evaluation is also limited given that no follow-up period is included. Whether habits indeed last over time and so facilitate behavioral adherence, cannot be confirmed without (or even with short) follow up periods [29].Third, in order to test our hypotheses participants will need to take part in many assessments, which might result in high attrition rates. We try to prevent dropouts by sending email reminders and keeping incomplete questionnaires available on the home screen under “open tasks”. Lastly, as the researcher(s) who analyze the data will also be involved in the data-collection process and in the study design, blinding of the analyst is not feasible. In the next step, the summative evaluation of the Habit coach app against a control group in a randomized controlled trial is warranted.

In sum, this trial addresses health care professionals’ adverse working and health conditions and acknowledges that health behavior change is a results of deliberative as well as non-deliberative psychological processes. Through a mobile app fostering healthy habit formation in the areas of physical activity, nutrition and mindfulness behaviors and theory-based strategies to support habit formation, shortcomings of previous research are overcome. The analyses and evaluation of the app will provide insights in the habit formation process supported by the app and will contribute to the mHealth literature in both theoretical and practical aspects.

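### The analysis is labelled intention-to-treat, but its inclusion rule makes it a completer analysis, which discards usable data and can bias the results

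*Protocol article*

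**What the plan says.** The Statistical analysis section first states: "Intention-to-treat analyses will be conducted, given that drop-out rates are usually high in eHealth research [80], per protocol analysis are not feasible". The next sentence defines the analysis set: "Only data sets from participants who completed the baseline, post and 50% of the weekly assessments will be included in the analysis". It applies to all five hypotheses.

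The same section plans to compare baseline scores between participants coded "0 = not retained for analysis, 1 = retained", with univariate tests and then logistic regression. It describes no analysis of the excluded participants' outcome data.

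On numbers, Statistical power asks for at least "228 participants (i.e., number of required individuals, accounting for 30% sample attrition". Under Strengths, challenges and limitations the authors warn that "participants will need to take part in many assessments, which might result in high attrition rates".

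On data collection, Evaluation design has all assessments completed in the app. Reminder e-mails go out for baseline and post only. For every other assessment the reminder is an entry in the app's list of open tasks.

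**The concern.** Readers take intention-to-treat to mean that everyone who entered the study is analysed, whatever they did afterwards. Here entry to the analysis depends on what participants did afterwards. With in-app forms and, between baseline and post, in-app reminders only, completing half the weekly forms requires continued use of the app. The rule therefore selects on engagement with the intervention.

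This matters more in a single-arm study. No control group passes through the same filter, so the hypothesis 1 changes rest directly on who is retained. If people whose habits develop poorly are likelier to stop answering, the retained group shows more change than the enrolled group. The associations in hypotheses 2 to 5 can also be distorted when retention depends on the outcome. The results would then be published under a label that tells readers this selection was avoided.

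**Working it through.** **1. Does the rule fit the label?** No. All three conditions (baseline, post, half the weekly forms) concern form completion, and two of them are met or failed after baseline.

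**2. Do the planned models need the rule?**

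| Hypotheses | Planned method | Data the method needs | Excluded although usable |
|---|---|---|---|
| 1 | Repeated-measures ANOVA, t-tests | Baseline and post | Both present, too few weekly forms |
| 2 to 4 | Hierarchical regression | Baseline predictors, post outcome | Both present, too few weekly forms |
| 5 | REML mixed model, 13 periods | Whatever waves exist | Weekly data present, post missing |

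The threshold is also not fixed. Evaluation design says "Additionally, 11 weekly assessments will be scheduled" (11/2 = 5.5, so 6 forms). The section on psychosocial determinants calls t1 to t13 weekly (13/2 = 6.5, so 7 forms).

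**3. How many are lost?** The 228 cannot be rebuilt, because the article does not state alpha, the intraclass correlation or the variance components. Its attrition step fits either 159/0.70 = 227.1 or 175 × 1.30 = 227.5, both rounding up to 228. The present point does not depend on which was used. Reading the 30% as the share failing the inclusion rule, 228 × 0.70 = 159.6. About 160 are analysed and about 68 excluded. The allowance protects power; it does nothing about selection.

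**4. How large could the bias be?** The documents give no link between retention and change, so this is an illustration only. Let change and the propensity to be retained be bivariate normal with correlation r, let p be the share retained, and let c be the standard normal quantile at 1 − p. Then

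bias in mean change (in SD of change) = r × φ(c)/p.

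For p = 0.70, φ(c)/p = 0.497. For p = 0.50 it is 0.798. With a true mean change of zero:

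| r (assumed) | Bias, 70% retained | Chance of a false improvement, n = 160 | Bias, 50% retained (assumed) |
|---|---|---|---|
| 0 | 0 | 2.5% | 0 |
| 0.1 | 0.05 SD | 9% | 0.08 SD |
| 0.2 | 0.10 SD | 24% | 0.16 SD |
| 0.3 | 0.15 SD | 47% | 0.24 SD |

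The third column is 1 − Φ(1.96 − bias × √160).

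**5. Does the planned attrition check repair this?** No. It compares baseline scores. It can flag measured baseline differences, but it neither corrects them nor detects selection on what happened after baseline. The stated contrast is with people who gave baseline data only, so partial completers are not clearly covered.

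**6. Would a mixed model on all data repair everything?** No. Automaticity is measured at baseline, interim and post, but with four items at the ends and two at interim. Health behaviours and health status are examined from baseline to post, and self-efficacy and action planning are listed for those two points only. Weekly intention and outcome expectancy are different single items on a 5-point scale.

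A simulation shows the consequence. Assumptions: true change 0.30, intercept variance 0.6, residual variance 0.4, slope SD 0.5, and dropout log-odds falling by 0.5 per unit of last observed change. With four waves, a likelihood analysis of all data recovers 0.30, as it must when dropout depends only on observed values. With the outcome seen only at baseline and post, and about 68% retained, completers give 0.37 and the likelihood analysis of all available data still gives 0.35. Most of the bias remains unless the intermediate information is brought in.

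**The case against.** The strongest case on the other side accepts that the label is wrong but disputes the harm.

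- **Direction and size.** A reader might infer that the hypothesis 1 changes will be overstated by a known amount. The documents do not support that. Nowhere do they say that people whose habits fail to grow stop answering; the limitations section ties attrition to the number of assessments. If retention is unrelated to change, there is no bias. This stands: the bias is possible and plausibly upward, but it is neither shown nor measurable from the article.
- **Simulations.** Dropout driven by the last observed change is missing at random by construction, so a mixed model must recover the truth. This stands. The simulated figures show the mechanism and the limits of the remedy, and say nothing about this trial's actual bias.
- **Hypotheses 2 to 5.** No calculation shows how far the associations would shift. This stands; the effect on them is stated only as possible.
- **Mitigation.** The plan allows for 30% attrition, compares retained with non-retained participants, and says that effectiveness cannot be evaluated without a control group. These limit what can be claimed from the results but do not correct the selection.
- **Evaluation design.** A reader might infer a second contradiction from "Outcome data will be the same for all participants, whether they continue or discontinue/deviate from the intervention protocol". That sentence concerns people who leave the intervention, whereas the inclusion rule concerns assessments. The two overlap in an app-based study but are not the same, so the point does not rest on it.

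An unseen analysis plan does not answer the point either, because the rule is stated outright in the article.

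**Conclusion.** The label and the rule contradict each other in adjacent sentences, and the analysis as written is a completer analysis. That conclusion needs no assumption. At the planned attrition about 160 of 228 participants would be analysed, and fewer if more than 30% fail the rule. The rule also excludes participants whose data are complete for hypotheses 1 to 4 or usable for hypothesis 5.

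The bias is conditional. It arises only if retention is related to change or, for the associations, to the outcomes. At 70% retention the illustration runs from 0 to 0.15 SD of change for assumed correlations of 0 to 0.3. The actual size cannot be derived from the document.

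**What to change.** 1. **Analysis set.** Replace the inclusion sentence with: the primary analysis includes all consenting participants with a baseline assessment.
2. **Hypothesis 5 and automaticity over time.** Use the REML mixed model on all available waves. State how four-item and two-item automaticity scores are made comparable.
3. **Outcomes measured only at baseline and post, and hypotheses 2 to 4.** Use multiple imputation drawing on baseline, interim and weekly data.
4. **Sensitivity to missing not at random.** Add an analysis in which non-completers are assumed to change less than the imputation model predicts, over a stated range. Items 2 and 3 are valid only under missing at random.
5. **Present set.** Keep it as a sensitivity analysis labelled completer, without the intention-to-treat label, and state whether half the weekly forms means half of 11 or half of 13.

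The cost is a wording change and modest extra analysis, with no additional participants or data. The downside is reliance on a missing-at-random assumption, which item 4 probes but cannot remove.

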### Objectives

The present study outlines the protocol for a longitudinal, multicenter single-arm study among health care professionals investigating the role of theory-based motivational and volitional predictors for healthy habit formation in daily life based on a mHealth intervention targeting physical activity, healthy nutrition and mindfulness behaviors (i.e., engaging in mindfulness techniques and relaxation exercises). The aim of this paper is to outline the study protocol including a detailed description of the mHealth intervention, the evaluation plan, and the study design. The main purpose of this trial is to understand the habit formation process for physical activity, nutrition and mindfulness behaviors and its predictors. As preliminary hypothesis (hypothesis 1 a-e), we expect to find positive changes from baseline to post assessments (i.e., 100 days post baseline) in: a) habit strength, b) motivational constructs (i.e., intention, outcome expectancies, self-efficacy), c) volitional constructs (i.e., action planning), d) health behavior (i.e., physical activity, nutrition, mindfulness behaviors) and e) health status (i.e., stress, back pain, well-being, physical and psychological health, body mass index). For the primary endpoint (habit strength over time) and to understand predictors of habit formation over time, we hypothesize that a) habit strength at post-assessment is predicted by baseline motivational and volitional constructs, controlling for baseline habit strength (hypothesis 2), b) that health behavior and c) health status at post assessment are predicted by motivational and volitional constructs as well as habit strength at baseline (hypotheses 3 and 4, respectively). Finally, we hypothesize that next-week habit strength will show positive associations with behavior-related motivational (5a) and volitional constructs over time (5b).

Additionally, we conduct a process evaluation by evaluating participants’ experiences and satisfaction with the app. For the process evaluation a mixed-methods approach will be applied involving questionnaires and structured interviews. The items addressed in this protocol paper are based on the 2013 Standard Protocol Items: Recommendations for Interventional Trials (SPIRIT) statement [[58]; see Additional file 1].

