### Health behavior

Changes in health behaviors is investigated from baseline to post assessments.

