### Health status

Changes in health status are examined from baseline to post assessments and mean values will be calculated to build each scale.

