### Strengths, challenges and limitations

Strengths. The mHealth intervention is theory driven and provides support during the entire behavior change process, starting with a motivational (i.e., goal setting), over a volitional (i.e., action planning) to habit formation and behavioral maintenance phase. Although mHealth interventions intended to increase physical activity and eating behaviors have shown positive effects, these effects often times were small and highly variable, caused by insufficient description of theoretical foundations and behavior change techniques used. The present study focuses specifically on mechanisms of action and respective behavior change techniques in order to predict change in behavior and make intervention design and evaluation more transparent and replicable. Furthermore, by allowing health care professionals to integrate the within-app mini interventions into their daily (work) routine, it is intended to tackle commonly reported problems of implementing programs such as massive disruption of the working day and attrition based on problems to fit interventions into daily routines outside the work context.

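### Hypotheses 3 and 4 leave out the baseline value of their own outcome, so their regressions cannot be read as predicting change in health behaviour or health status

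*Protocol article*

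**What the plan says.** The Objectives section states hypothesis 2 as: "habit strength at post-assessment is predicted by baseline motivational and volitional constructs, controlling for baseline habit strength (hypothesis 2". It then turns to health behaviour and health status, ending: "health status at post assessment are predicted by motivational and volitional constructs as well as habit strength at baseline (hypotheses 3 and 4, respectively". Adjustment for the starting value of the outcome is written into hypothesis 2 and is absent from hypotheses 3 and 4.

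The Statistical analysis section covers all three hypotheses with one specification: hierarchical multiple linear regression "with motivational, volitional and habit-related predictors at baseline to predict habit strength, health status and health behavior at post-assessment". For hypothesis 2, the habit predictor is the baseline outcome. For hypotheses 3 and 4 it is a different variable, and no baseline behaviour or health term is named.

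The missing covariates exist. Under Health behavior: "Changes in health behaviors is investigated from baseline to post assessments". Under Health status: "Changes in health status are examined from baseline to post assessments".

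The Strengths, challenges and limitations section says the study focuses on mechanisms of action and behaviour change techniques "in order to predict change in behavior and make intervention design and evaluation more transparent and replicable".

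**The concern.** A participant who is already active may well report stronger intention, self-efficacy and habit at entry, and may still be the more active one 100 days later. A regression of the post value on those baseline scores then finds an association even if none of them says anything about who changes. Without the baseline outcome in the model, a carried-forward cross-sectional correlation and prediction of change cannot be told apart.

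The study has no control group, and the article concedes that it cannot evaluate effectiveness. The predictor analyses therefore carry much of what the trial can contribute. At stake is a report naming determinants of behaviour change or health improvement that predict no change at all.

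**Working it through.** **Inputs from the article.** The Statistical power section gives 228 "participants (i.e., number of required individuals, accounting for 30% sample attrition". That implies 228 × 0.70 = 159.6, so about 160 analysed. The 228 was set for the mixed model of automaticity over time. It cannot be rebuilt here, because the significance level and variance components are not given, and it is not disputed. The instrument descriptions give six predictors per behavioural domain: intention, positive and negative outcome expectancies, self-efficacy, action planning and automaticity.

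**Assumed inputs (none is in the article).**
- Two-sided level of 5%.
- Correlation s between baseline and post outcome: 0.5 to 0.7.
- Correlation r of each predictor with the baseline outcome: 0.2 to 0.4, with 0.1 as a weak case.
- Correlation ρ among predictors: 0.3 to 0.5.
- No predictor has any effect on the post outcome once the baseline outcome is known.

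**Step 1: one predictor, baseline outcome omitted.** The implied correlation with the post outcome is r × s. At r = 0.3 and s = 0.6 it is 0.18. The Fisher approximation gives z = atanh(0.18) × √157 = 2.28, so rejection is about Φ(2.28 − 1.96) = 63%. At s = 0.6, the rates for r = 0.1, 0.2, 0.3 and 0.4 are about 12%, 33%, 63% and 87%. Over the assumed range they run from 24% (r = 0.2, s = 0.5) to 95% (r = 0.4, s = 0.7). Simulation agrees to within about a percentage point.

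**Step 2: six predictors, joint test.** R² = 6(rs)² / (1 + 5ρ), with noncentrality λ = 160 × R² / (1 − R²) on 6 and 153 degrees of freedom.

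| r | s | ρ | R² | λ | Rejection |
|---|---|---|---|---|---|
| 0.2 | 0.5 | 0.5 | 0.017 | 2.8 | 19% |
| 0.3 | 0.6 | 0.5 | 0.056 | 9.4 | 59% |
| 0.3 | 0.6 | 0.3 | 0.078 | 13.5 | 78% |
| 0.4 | 0.7 | 0.3 | 0.188 | 37.1 | over 99% |

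**Step 3: six predictors, single coefficients.** The predictors share the spurious signal, so each coefficient is inflated far less. The standardised slope is rs / (1 + 5ρ). At r = 0.3, s = 0.6 and ρ = 0.3 it is 0.18 / 2.5 = 0.072. The variance inflation factor is (1 + 4ρ) / [(1 − ρ)(1 + 5ρ)] = 2.2 / 1.75 = 1.26, so the standard error is √(0.922 × 1.26 / 153) = 0.087. The ratio is 0.83 and rejection is about 13%. With ρ = 0.5 it is about 8%. Over the whole range it is about 6% to 27%.

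**Step 4: weak correlation.** At r = 0.1, all three forms of test reject in about 5% to 14% of studies.

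**Step 5: baseline outcome entered first.** In simulation, the R-squared-change test for the six predictors, and the test of a single predictor, reject in about 5% throughout.

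**Step 6: baseline measured with error.** Suppose a fully stable trait is measured with test-retest correlation 0.6, and the predictor correlates 0.3 with each measurement. The partial correlation given the observed baseline is (0.3 − 0.3 × 0.6) / √(0.91 × 0.64) = 0.12 / 0.763 = 0.157. The adjusted single-predictor test still rejects in about 52% of studies, against about 97% unadjusted (correlation 0.3, n = 160).

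**The case against.** The strongest reply is that hypotheses 3 and 4, as worded, concern the level at post-assessment, not change. In every scenario above the predictor does correlate with the post outcome, so rejecting is correct for that question. This stands. A reader might infer that the plan tests its stated hypotheses at the wrong error rate, and the documents do not support that. The fault lies in reading the result as prediction of change. The sentence that invites this reading is in the Discussion and does not name hypotheses 3 or 4.

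Second, a single-predictor calculation overstates what happens to individual coefficients in the planned multiple regression. This also stands (step 3), but the joint test stays heavily inflated, so moving to several predictors does not remove the problem.

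Third, no correlations are given. Health status includes body mass index, back health and perceived stress, whose link to domain-specific intention may be weak. So one cannot say that predictors will look significant, only that they can.

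Fourth, an article condenses, and hierarchical entry leaves room for a baseline block. That carries less weight. The predictor set is stated in two sections, and hypothesis 2 shows that the authors write baseline control where they intend it.

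**Conclusion.** The point holds in limited form. As stated, the models for hypotheses 3 and 4 cannot separate prediction of change from correlation present at entry, although hypothesis 2 is built to do so and the needed covariates are collected.

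The inflation depends on two assumed quantities: how stable the outcome is over 100 days and how strongly the predictors correlate with it at baseline. Within the ranges used it is large for joint tests and single-predictor models, modest for individual coefficients, and small when the correlation is 0.1. If fewer than 160 are analysed, the rates fall somewhat. At 228, the single-predictor rates for s = 0.6 and r = 0.2, 0.3 and 0.4 would be 44%, 78% and 96%.

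Two further readings are tempting and unsupported. The primary endpoint is not touched, because hypothesis 2 adjusts for baseline habit strength and hypothesis 5 uses mixed models of habit strength. Nor is baseline adjustment a complete cure: the 5% figure requires an error-free baseline, and these outcomes are self-reported.

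**What to change.** In the hierarchical regressions for hypotheses 3 and 4, enter the baseline value of the same behaviour or health measure as the first block. Then enter the motivational, volitional and habit blocks and test each by R-squared change. Add to both hypotheses that they control for the baseline value of the outcome, in line with hypothesis 2. State as a limitation that error in self-reported baselines leaves some residual confounding. If the unadjusted association with the post level is also of interest, report it separately and call it prognosis of level.

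The cost is one degree of freedom per model, no new data, and a short edit to the Objectives and Statistical analysis sections. The hypotheses are registered and were already refined by one amendment, so the rewording should be reported to the register, as the Ethical approval section provides. Analysis begins only after data collection is complete, so the change can be made before results are seen.
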